### Randomization and blinding

To minimize the potential bias of individual differences or covariates, eligible participants will be recruited and randomly assigned to either a multi-domain exercise group or an online educational courses control group with a 1:1 allocation ratio using a computerized permuted block randomization algorithm with stratification (Lim and In, 2019). Additionally, the randomization will be stratified by *ApoE* genotype (High-risk: *ApoE* ε3/ε4 and *ApoE* ε4/ε4 vs. Low-risk: *ApoE* ε2/ε2, *ApoE* ε2/ε3, *ApoE* ε2/ε4, and *ApoE* ε3/ε3) to confirm equal allocation to both groups based on these criteria.

The randomization list for the assignment sequence will be created using the IBM SPSS Statistics for Windows (SPSS Inc., Chicago, IL, USA). Except for staff involved in the multi-domain exercise program and online educational program, assessors and data analyzers will be kept blind to participants' group assignments.

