### Participants

To ensure a sufficient sample size, the sample size calculation for the current study was conducted using G^*^Power version 3.1.9.4 (ANOVA; repeated measures, within-between interaction). Multiple recruitment strategies will be utilized, including online social media advertising and word-of-mouth referrals, as well as posters and flyers placed or distributed in local community centers and organizations. Finally, individuals from previous studies will also be screened for recruiting potential participants. Before participating in the current study, potential participants will be screened by phone, followed by an on-site interview to ensure they meet the inclusion criteria.

Eligible participants (half of them are *ApoE* ε3/ε4 or *ApoE* ε4/ε4 carriers) will be provided sufficient information, and informed consent relating to the study will be provided prior to the initiation of the study. Recruitment, enrollment, and randomization will occur on a rolling basis. Finally, a total of 100 community-dwelling, cognitively healthy adults aged 45–70 years who are able to participate in moderate-intensity exercise will be recruited in a 1-year time period in Taipei, Taiwan. The inclusion and exclusion criteria are detailed in Table 1.

**Table 1 T1:** Inclusion and exclusion criteria for participating in the study.

**Inclusion criteria**	**Exclusion criteria**
- Adults aged from 45 to 70 years	- Diagnosed or self-reported cognitive problems (e.g., mild cognitive impairment or dementia)
- Normal or corrected-to-normal vision	- The diagnosed or self-reported physical disease (e.g., untreated hypertension and chronic heart disease, stroke, brain tumor, musculoskeletal disorders, other exercise contradictions)
- Able to speak and read Chinese	- Diagnosed or self-reported major psychiatric illness (e.g., major depression, schizophrenia)
- Scores of MMSE ≥ 25	- Diagnosed or self-reported neurodegenerative disease (e.g., AD and other dementias, PD and PD-related disorders, Huntington's disease)
- PAR-Q score = 0	- History of severe alcohol or drug abuse
- Able to conduct the exercise with moderate intensity	- History of chemotherapy
- Meet the criteria to undergo MRI	- Unable to complete the MRI scan
	- Traveling consecutively for 3 weeks or more during the study
	- Unwillingness to be randomized to one of the two groups
	- Currently participating in another study trial

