### Statistical analysis

To address whether the 6-month multi-domain exercise program affects working memory or episodic memory performance and brain functioning, we will employ a two-way repeated-measure analysis of variances (ANOVA) of mixed design with group status (i.e., multi-domain exercise group vs. control group) as the between-subject variable and time points (i.e., Baseline-Assessment vs. Post-Assessment) as the within-subject variable, with the Greenhouse–Geisser correction, where deemed appropriate. The two-way ANOVA will be employed individually for each primary outcome. Multiple *t*-test comparisons will be conducted as follow-up by setting the familywise alpha levels at 0.05, prior to a Bonferroni correction.

To address the moderating role of *ApoE* genotype on the effect of the multi-domain exercise program on working memory and episodic memory performance, as well as brain function assessed from neuroimaging metrics, we will employ the three-way repeated-measure ANOVA of mixed design with group status as the between-subject variable, and *ApoE* genotype [i.e., high-risk candidates (*ApoE* ε3/ε4 and *ApoE* ε4/ε4) vs. the low-risk candidates (*ApoE* ε2/ε4, *ApoE* ε2/ε3, *ApoE* ε2/ε2, and *ApoE* ε3/ε3)] and time points as the within-subject variable, with a Greenhouse–Geisser correction where deemed appropriate. In addition, multiple *t*-test comparisons will be conducted as follow-ups by setting the familywise alpha levels at 0.05 prior to a Bonferroni correction.

To address whether the effects of the multi-domain exercise program on working memory, episodic memory, and brain function are mediated by physical fitness and BDNF, we will employ Pearson product-moment correlations to examine relationships between change in physical fitness, BDNF, and the primary and secondary outcomes. Separate mediation analyses will be conducted using PROCESS software for SPSS. Statistical significance of mediators will be considered if the 95% bias-corrected bootstrap confidence interval (5,000 bootstrap samples) does not include zero. For all analyses, age, sex, BMI, and educational levels will be controlled for, and the alpha value will be set at 0.05, prior to statistical adjustment for all analyses.

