Several challenges of this study are worth mentioning. For instance, the current trial will recruit 50 cognitively healthy participants with a genetic risk for AD. Nevertheless, the recruitment of sufficient participants is challenging, given that the prevalence of *ApoE* ε4 allele(s) in Taiwan is only around 20% (Hong et al., 1996; Wang et al., 2011). Unfortunately, this challenge will be further escalated by the occurrence of the COVID-19 pandemic. Although this challenge might be partially alleviated through recruiting *ApoE* ε4 allele(s) carriers from our previous research and the progressive ease of the COVID-19 pandemic in Taiwan, we still expect the inclusion of a sufficient number of participants, especially the *ApoE* ε4 allele(s) carriers, will be difficult. Drop-out and adherence will be other challenges in the current study. Two strategies will be applied to curtail these challenges. First, frequent contacts and regular newsletters will be delivered to all participants from the research group. Furthermore, the multi-domain exercise group can attend two out of 10 optional exercise sessions each week instead of adhering to a fixed exercise schedule. These approaches enhance the personal connection to the study and provide user-friendly access to the exercise program, and we expect this to enhance participants' adherence and minimize the risk of them withdrawing from the intervention (Robiner, 2005). Finally, the current trial collects a considerable amount of outcome measures, and many of them have to be collected in a time-sensitive manner. For instance, to accurately reflect the relationships between physiological conditions and brain health, physical fitness, BDNF levels, cognitive tasks, and fMRI assessments will be completed within 3 weeks before and after the 6-month exercise program, respectively. To overcome this potential challenge, a limited number of participants (e.g., five people) will be grouped as one intervention unit, and the unit will coordinate the most suitable time for initiating the assessments and exercise program.

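### The primary ANOVA omits ApoE risk, the factor that stratifies randomisation, so its group × time test is slightly conservative if ApoE predicts change

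*Protocol article*

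**What the plan says.** **Allocation.** Under Randomization and blinding, participants are assigned "with a 1:1 allocation ratio using a computerized permuted block randomization algorithm with stratification". The stratification factor is named there: "Additionally, the randomization will be stratified by *ApoE* genotype". High risk is ε3/ε4 or ε4/ε4. Every other genotype, including ε2/ε4, counts as low risk.

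**Enrolment.** Under Participants, "half of them are *ApoE* ε3/ε4 or *ApoE* ε4/ε4 carriers". The Discussion gives the count as 50, the total being 100. It also says that the prevalence of the ε4 allele(s) "in Taiwan is only around 20" per cent.

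**Primary analysis.** Under Statistical analysis, the mixed ANOVA takes "group status (i.e., multi-domain exercise group vs. control group) as the between-subject variable" and time as the within-subject variable. "The two-way ANOVA will be employed individually for each primary outcome". The adjustment set is stated once for everything: "For all analyses, age, sex, BMI, and educational levels will be controlled for". ApoE appears in neither place.

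**ApoE analysis.** A separate three-way ANOVA (group, ApoE, time) on the same outcomes addresses moderation.

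**The concern.** Stratified allocation makes the two arms more alike on ApoE than chance would. The true sampling variance of the group comparison therefore excludes the between-stratum part. A model without the stratum still counts that part as noise, so its standard error is too large and its test too cautious.

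This is not a detail left for later, because the article names the covariates for all analyses and the stratification factor is not among them. The Background links ε4 with faster cognitive decline, so an association between ApoE and change over six months is plausible by the plan's own account.

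A second point concerns reporting. The pooled effect averages over a sample that is half high risk by design, while the closing summary speaks of people in this age range without reference to genotype. A reader could take the pooled figure as applying to the general population of that age.

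**Working it through.** **The plan's own figure.** The documents give no figure for the effect of adjusting for ApoE. The nearest is N = 100, from g = 0.30, power 0.80 and alpha 0.05. With f = 0.30/2 = 0.15, two groups, two time points and an assumed pre-post correlation of 0.5, the noncentrality is N·f²·m/(1 − ρ) = 100 × 0.0225 × 2/0.5 = 9. That gives power 0.844 at N = 100, and N = 90 suffices for 0.80. N = 100 then follows from 90/(1 − 0.10) if 10% dropout is allowed. Neither the correlation nor a dropout rate is stated. The point below does not depend on them.

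**Step 1: type I error.** With two time points, the group × time test is a comparison of change scores. A constant ApoE difference in level cancels, and only ApoE-related change matters. Let R² be the share of change-score variance that ApoE explains (assumed; the documents give no value). With balanced strata:

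- true SE / model SE = √(1 − R²)
- true alpha = 2·[1 − Φ(1.96/√(1 − R²))]

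**Step 2: power.** Take a difference of 0.3 change-score SD with 50 per arm. The SE is √(4/100) = 0.2, so the standardised effect is 0.3/0.2 = 1.5.

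- without ApoE: Φ((1.5 − 1.96)/√(1 − R²))
- with ApoE: Φ(1.5/√(1 − R²) − 1.96)

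| R² (assumed) | SE ratio | True alpha | Power without ApoE | Power with ApoE | Loss |
|---|---|---|---|---|---|
| 1% | 0.995 | 0.049 | 0.322 | 0.326 | 0.004 |
| 5% | 0.975 | 0.044 | 0.319 | 0.337 | 0.018 |
| 10% | 0.949 | 0.039 | 0.314 | 0.352 | 0.039 |

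The power level here is lower than the plan's because a change-score difference of 0.3 SD has noncentrality 1.5² = 2.25, not 9. Putting √9 = 3 in place of 1.5 in the same formulas gives losses of 0.002, 0.011 and 0.022, so the loss is small on either reading.

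**Step 3: does the omission move the estimate?** In 2,000 simulated trials (N = 100, 25 per cell, true effects 0.5 SD in high risk and 0.1 SD in low risk), the mean group effect was 0.295 in each of three models: without ApoE, with ApoE as a main effect, and with an effect-coded ApoE × group term. Trial by trial, the three estimates agreed to rounding error. The model term changes the standard error, not the estimate or its weights.

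**Step 4: what the pooled effect averages.** At a high-risk share p, the average effect is p·d_high + (1 − p)·d_low. Enrolment sets p = 0.5. Against p = 0.2 the gap is (0.5 − 0.2)·(d_high − d_low) = 0.30·(d_high − d_low). Illustrations with assumed effects:

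- 0.3 and 0.3: no gap
- 0.5 (high) and 0.1 (low): 0.30 against 0.18
- 0.1 (high) and 0.5 (low): 0.30 against 0.42

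If the quoted 20% is an allele frequency, carriers are 1 − 0.8² = 36%, and 0.18 becomes 0.244.

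**The case against.** **The cost is small and falls on the safe side.** This stands. Leaving out a balanced stratum cannot inflate false positives, and the power loss reaches about 0.04 only if ApoE explains 10% of change-score variance.

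**ApoE is already analysed.** This stands in part. The three-way ANOVA is the right place for stratum-specific effects. It does not correct the error term of the primary two-way test. A non-significant interaction there would also say little: with 25 per cell its SE is √(4/25) = 0.4 change-score SD, so power is about 0.12 for a stratum difference of 0.3 SD and 0.32 for 0.6 SD.

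**A stronger reading is tempting.** A reader might infer that leaving ApoE out is what produces a 50:50 average, that the primary estimate is therefore biased for a population with about 20% carriers, and that it should be reweighted 0.2 to 0.8. The documents do not support this, for four reasons:

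- The 50:50 weighting comes from enrolment, and adding ApoE leaves it unchanged (Step 3).
- No population-average target is declared. Study design and the Discussion describe adults with and without genetic risk, and for the enrolled mix the estimate is unbiased. The direction of any moderation is also left open.
- The 20% may mean carriers or allele frequency, and the high-risk stratum excludes ε2/ε4, so fixed weights have no firm basis.
- A 20:80 contrast has (0.2² + 0.8²)/(0.5² + 0.5²) = 0.68/0.50 = 1.36 times the variance. It would still not make a volunteer, MRI-eligible Taipei sample representative.

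**Conclusion.** The point holds as a minor inefficiency in the primary model together with a reporting clarification. The stratification factor is missing from both the primary ANOVA and the stated covariate list. If ApoE explains 1% to 10% of change-score variance, the nominal 0.05 test runs at about 0.049 to 0.039 and gives up about 0.004 to 0.04 in power. If ApoE does not predict change, nothing is lost. These figures assume balanced strata, a normal approximation and R² values that the documents do not supply, and they ignore variance already removed by the listed covariates.

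The estimate is not biased for the sample enrolled. The enrichment affects only how far the pooled effect can be generalised, and only if ApoE modifies the effect.

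**What to change.** 1. Add ApoE stratum (high/low) as a between-subject factor, with its interaction with time, to every primary model, and name it beside age, sex, BMI and education. The time interaction is the part that matters, because a main effect alone does not enter the group × time error term.
2. State that the pooled effect refers to an enriched sample, planned as half high risk.
3. Report group effects by stratum with confidence intervals from the planned group × ApoE × time analysis. ApoE has to be fitted there as a between-subject factor; the current sentence places it with time as within-subject, although genotype is fixed for each person.
4. Word the general conclusions in the closing summary to match the enriched sample.

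Cost: one model term and its time interaction, one degree of freedom in the group × time test, and a few sentences of reporting. No additional participants or data are needed, since ApoE is genotyped before randomisation.

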### Intervention protocols

Eligible individuals will participate all together in either the multi-domain exercise group or the control group for 6 months.

#### Multi-domain exercise group

The exercise program for the multi-domain exercise group is designed by senior academic psychologists with input from a team of professional exercise experts experienced in working with late middle-aged and older adults. The multi-domain exercise group consists of a 6-month intervention, including one 90-min on-site and several online sessions, for up to 60 min per week. The program primarily focuses on multiple exercise modalities (i.e., aerobic exercise, resistance exercise, and coordinative exercise), with two additional lifestyle domains (i.e., meditation and social interaction). Specifically, each exercise course includes five stages:

Stage 1: 15 min of warm-up and aerobic exercise.Stage 2: 25 min of resistance and flexibility exercise from the “Western exercise” perspective.Stage 3: 30 min of the main exercise, named as Bagua Daoyin, consisting of resistance exercise, coordination, and flexibility exercise from the “Eastern exercise” perspective. This exercise, including eight forms of sequential movements, emphasizes muscular strength and endurance of the upper and lower trunk, trunk rotation, weight shifting, and coordination of visual and musculoskeletal systems. Additionally, awareness of the proprioception with mental focus from different parts of the body will be heightened.Stage 4: 10 min of social interaction exercise. The exercise program will take place in a group format, and practice in pairs or small groups will be frequently encouraged, providing sufficient social interactions among participants.Stage 5: 10 min of cool down and meditation. After the cessation of the main exercise session, a cool down and mindfulness-based meditation will be conducted. The mindfulness-based meditation is based on a mindfulness program utilized previously, focusing on the components of mindful breathing, awareness, nonjudgement, and acceptance (Nien et al., 2020).

Each on-site exercise course will be conducted at one recreational center in Taipei, Taiwan, supervised by experienced exercise instructors, who will instruct the movements designed for the multi-domain exercise program.

#### Control group

The control group will not receive any exercise program and will be informed to maintain their lifestyles. In addition, participants will be invited to attend one 60-min online group educational course regarding the effects of exercise on cognitive function and general instructions for cognitive promotions per week to eliminate the experimental expectation effect. The participants will be required to provide their physical activity behavior once per month for 6 months (see Figure 2). After data collection at the Post-Assessments, the participants can voluntarily join the multiple-domain exercise program for the next 3 months as compensation for their participation.

### Assessments and outcome measures timeline

All participants will undergo multiple assessments before (Baseline-Assessments) and after (Post-Assessments) the intervention. The Baseline-Assessments will be organized into two assessment days (ADay) in the following order: (1) ADay_1_: psychosocial measures, blood extraction, and physical fitness assessment, and (2) ADay_2_: fMRI scans. The same assessment order (ADay_3_ and ADay_4_) will be carried out in the Post-Assessments. Assessments will be carried out at National Taiwan Normal University, and fMRI scans will be performed in the Imaging Center for Integrated Body, Mind, and Culture Research in National Chengchi University, Taipei, Taiwan, within 3 weeks of completion of the initial screening and the cessation of the 6-month intervention (Table 2). The timeline for the trial is visualized in Figure 3.

**Table 2 T2:** Assessments.

	**Recruitment**	**Baseline-assessments** **(**<**3 weeks before the intervention)**		**6-month intervention**			**Post-assessments** **(**<**3 weeks after the** **intervention)**	
	Screening	**ADay** _ **1** _	**ADay** _ **2** _	Initial intervention	Middle intervention	Final intervention	**ADay** _ **3** _	**ADay** _ **4** _
Information of study	**X**							
Review of criteria	**X**							
Medical history, General health status, MMSE, PAR-Q	**X**							
Informed consent form	**X**							
Battery of psychosocial measures	**X**						**X**	
Blood extraction		**X**					**X**	
Battery of physical fitness tests		**X**					**X**	
Magnetic resonance imaging			**X**					**X**
rs-fMRI								
fMRI: n-back task, RISE task								
Attendance				**X**	**X**	**X**		

ADay, Assessment days; MMSE, Mini-Mental Status Examination; PAR-Q, Physical Activity Readiness Questionnaire; rs-fMRI, resting-state functional magnetic resonance imaging; RISE, relational and item-specific encoding.

**Figure 3 F3:**
[figure not shown]
Experimental timeline. ADay_1_, ADay_2_, ADay_3_, and ADay_4_, assessment day 1 to assessment day 4, respectively; BDNF, brain-derived neurotrophic factor; fMRI, functional magnetic resonance imaging; MDE, multi-domain exercise; PF, physical fitness assessments; PsySoc, psychosocial measures; rs-fMRI, resting-state functional magnetic resonance imaging.

### Primary outcome assessments

#### N-back working memory task

A modified n-back working memory task (Li et al., 2014) will be programmed using E-Prime to examine participants' working memory. The n-back task contains a sequence of single-digit numbers (i.e., 1–9) presented with a duration of 500 ms and a fixed inter-stimulus interval of 2,000 ms. All participants will be instructed to respond if the current stimulus matches the one from *n* steps earlier in the sequence. In addition, all participants will be required to respond by pressing a button on a standard keyboard when the stimulus matches and pressing another button when the stimulus does not match. Both 1-back and 2-back conditions will be included in the task. A total of four blocks with 16 trials will be conducted, in which the stimuli will appear in random order. The total task time is about 7 min, and reaction time and accuracy will be recorded as indices of behavioral performance.

#### Relational and item-specific encoding task

The computerized Relational and Item-Specific Encoding (RISE) task is modified from the original RISE task (Ragland et al., 2012, 2015; Erickson et al., 2019) and will be utilized to assess episodic memory. Briefly, the task consists of two phases. During the first phase (i.e., the encoding phase), pairs of item-specific objects or relational objects will be alternatively presented. Participants will be instructed to identify whether the object is living or nonliving (item-specific encoding response trials) or whether one item could fit inside the other item in real life (relational encoding response trials). During the second phase (i.e., the recognition phase), participants will determine whether the item has been presented previously or never presented (item recognition). Stimuli will be presented for 3 and 2 s for the encoding phase and item recognition phase of the task, respectively, and participants are encouraged to respond as quickly and accurately as possible. The total task duration will be ~30 min. Reaction time and accuracy during both encoding and recognition phases will be recorded as the indices of behavioral performance.

#### Functional magnetic resonance imaging acquisition and analysis

All participants will undergo a series of whole-brain functional magnetic resonance imaging (fMRI) before and after the intervention. The data acquired will include resting-state fMRI (rs-fMRI) and task-evoked fMRI using a Siemens 3.0 T MRI scanner (Magnetron Prisma, Siemens, Germany) with a 32-channel head coil at the Imaging Center for Integrated Body, Mind, and Culture Research in National Chengchi University, Taipei, Taiwan. The parameters for MRI screening will be adapted from previous studies (Castells-Sánchez et al., 2019; Erickson et al., 2019).

